### Data collection

Data will be collected between December 2018 and December 2019, conducted over 12 months of intervention delivery and follow-up. The data obtained in this study will be registered in an electronic database. The effectiveness of the continuing education program will be assessed before and after the intervention. The same questionnaires will be used in T0 and T12 for the pharmacy staff and the patients or caregivers. An additional measurement will be made for the intervention group 12 months after the end of the follow-up time in order to evaluate the effects of the educational intervention over time. All measuring instruments will be reviewed and adjusted by a group of 10 experts. Three different sessions will be carried out, in which the questionnaire will be presented, and the experts will be asked for their opinions regarding the relevance of the content of the items (content validity).

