#### Community pharmacy staff competencies (knowledge, skills, and attitudes)

For the measurement of knowledge, a self-applied questionnaire of 50 multiple-choice questions (4 possible answers) with only one answer was constructed, and it will be categorized as correct or incorrect. The questionnaire will have the following topics: (1) pharmaceutical terminology and basic pharmacology, (2) pharmaceutical legislation, (3) technical and administrative management of the pharmacy, (4) communication and health education from the pharmacy, (5) good practices of dispensing and proper use of medicines, (6) pharmacovigilance from the pharmacy, and (7) pharmaceutical intervention on some common diseases in pharmacy (depression, anxiety disorder, sleep disorders, and pain management).

For the measurement of skills and attitudes, a self-applied questionnaire of 100 questions or performance criteria was constructed, which will be evaluated according to the frequency in which it will perform. For this purpose, a Likert scale will be established with four possible options: never (1), sometimes (2), usually (3), or always (4) that evaluate the following competencies—(a) provision of patient care: initial contact with the patient, medical prescription, medication needs, medication reconciliation, medication supply, use of guidelines and protocols, drug specifications, drug interactions, information about medications and patient education, additional activities, identification of drug-related problems, patient care, and evaluation of results; (b) personal: personal organization, practical communication skills, teamwork, and professionalism; (c) problem-solving: access related to information, knowledge, information analysis, and monitoring the patient; and (d) management and organization: clinical management and pharmacological safety, service provision, acquisition, and satisfaction of the services offered.

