### Statistical methods

Baseline and demographic characteristics will be analyzed descriptively. All primary and secondary outcomes will be compared in pre-post analyses and between-group comparisons. Comparisons for categorical variables will be conducted by using the chi-square test (or the Fisher exact test when appropriate). For continuous variables, we will use the independent sample *t* test (if the distribution is not normal, we will use the Mann-Whitney *U* test). Student’s *t* test will be used to compare means and odds ratios (ORs), and 95% confidence intervals (CIs) will be estimated as well. ORs will be used with the data reported from the knowledge questionnaire, to establish the association between receiving or not receiving the intervention and improving or not knowing. Spearman’s correlation will be used to identify the association for test and re-test reliability. Multivariable analyses will be performed to explain the association of multiple variables with the factors significantly related to the primary outcome (such as the job profile of the pharmacy staff, and others that will be considered as relevant variables). The McNemar tests will be used to analyze the difference in scores of the competency’s questionnaire of skills and attitudes and the scores of the knowledge questionnaire. All statistical tests will be computed using the Statistical Package for the Social Sciences (version 23; SPSS, Chicago, IL, USA) with significance defined as a *p* < 0.05.

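### McNemar tests are assigned to questionnaire scores that are not binary, and the article does not say that the planned between-group comparison, rather than the pre-post tests, decides effectiveness

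*Protocol article*

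**What the plan says.** The Outcomes section makes staff competencies the primary outcome, measured at T0 and T12 with two self-applied questionnaires and supplemented by simulated patients.

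- **Knowledge.** The competencies section describes "a self-applied questionnaire of 50 multiple-choice questions (4 possible answers) with only one answer was constructed", each answer being marked right or wrong.
- **Skills and attitudes.** There are 100 performance criteria, for which "a Likert scale will be established with four possible options: never (1), sometimes (2), usually (3), or always (4").
- **Test tied to these questionnaires.** Statistical methods says "The McNemar tests will be used to analyze the difference in scores of the" skills/attitudes questionnaire and the knowledge questionnaire.
- **Comparisons promised in the same section.** "All primary and secondary outcomes will be compared in pre-post analyses and between-group comparisons". The tests listed are generic: "Comparisons for categorical variables will be conducted by using the chi-square test (or the Fisher exact test when appropriate"), and "For continuous variables, we will use the independent sample *t* test", with Mann-Whitney as the alternative. For knowledge only, odds ratios are planned "to establish the association between receiving or not receiving the intervention and improving or not knowing".
- **How effectiveness is described.** Data collection says "The effectiveness of the continuing education program will be assessed before and after the intervention".
- **Sample size.** 30% improvement is expected in the intervention group against 15% in control, giving 121 pharmacies per group, or 135 after a 10% allowance for losses.

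**The concern.** There are two linked problems.

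First, the test does not match the data. McNemar's test compares the two kinds of switch, no-to-yes and yes-to-no, in a paired binary outcome. A count of correct answers out of 50 is not binary, and neither is a score built from 100 four-level items. For skills/attitudes, McNemar is the only test that Statistical methods ties to the questionnaire by name. Pre-post analyses are promised for every outcome, yet no paired method suited to a score is named.

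Second, a pre-post test within one arm does not answer the question of a parallel-group superiority trial. The plan itself expects controls to improve, uses the same questionnaires at T0 and T12, and has the same researcher visit both groups, which also both receive calls. Change in the intervention arm can therefore be significant without any programme effect. The article lists within-arm and between-arm tests together without saying which decides the primary outcome, so a within-arm result could later be presented as evidence of effectiveness.

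**Working it through.** **1. Does the test fit?**

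| Quantity | Form | McNemar applicable? |
|---|---|---|
| One knowledge item, T0 and T12 | right/wrong | Yes |
| Knowledge score | 0 to 50 if correct answers are counted | No, unless dichotomised |
| One skills/attitudes item | four ordered levels | No |
| Skills/attitudes score | 100 to 400 if items are summed (assumption; the article does not state the scoring) | No, unless dichotomised |

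The article applies the test to scores, the second and fourth rows. Applied instead item by item to knowledge, it would give 50 tests per arm.

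**2. The plan's own figure.** Inputs from Sample size: p1 = 0.30, p2 = 0.15, 95% confidence (taken as two-sided, z = 1.960), 80% power (z = 0.842), 1:1 allocation. The pooled-variance formula for two proportions, without continuity correction, is

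n = [1.960·√(2·p̄(1−p̄)) + 0.842·√(p1(1−p1)+p2(1−p2))]² / (p1−p2)², with p̄ = 0.225.

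- First term: 1.960 × √0.34875 = 1.157
- Second term: 0.842 × √0.3375 = 0.489
- n = (1.646)² / 0.0225 ≈ 120.5, so 121
- Losses: 121/0.9 = 134.4, so 135

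Both figures reproduce exactly, and power at 121 is 80.2%. The trial is therefore sized on a between-arm contrast of proportions improving, not on a pre-post change.

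**3. What a within-arm McNemar result shows when the programme does nothing.** Let b be the number who improve and c the number who worsen in one arm. The exact two-sided p-value is 2·P(X ≤ min(b, c)), with X ~ Binomial(b+c, ½).

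One example for the control arm, with 121 pharmacies and one result each: 15% improving is about 18 and an assumed 5% worsening is about 6. Then b+c = 24, P(X ≤ 6) = 190,051/16,777,216 = 0.01133, and p = 0.0227. The control material would look effective by this test.

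Over a range: 5,000 simulated trials per row, 121 per arm, 15% improving in both arms. The between-arm test compares proportions improved, z = |p̂1−p̂2| / √(p̄(1−p̄)·2/121), which is equivalent to the uncorrected chi-square test. Clustering is ignored.

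| Assumed worsening, both arms | McNemar significant, intervention / control | Between-arm test significant |
|---|---|---|
| 0% | 100% / 100% | 4.9% |
| 5% | 63.7% / 64.2% | 5.1% |
| 10% | 14.3% / 14.7% | 5.1% |

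As a check, with 30% against 15% improving and 5% or 10% worsening, the same between-arm test is significant in 80.0% and 80.5% of simulated trials, in line with the planned power.

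**The case against.** The strongest reply is that the trial does not rest on McNemar. Statistical methods promises between-group comparisons for all primary and secondary outcomes, lists tests for them, and plans an odds ratio of improving in knowledge by group. The trial is declared a superiority trial, and its sample size is a between-arm calculation. The before-and-after sentence stands under Data collection, next to the statement that the same questionnaires are used at T0 and T12, so it can be read as measurement timing. All of this stands. A reader might infer that effectiveness is to be judged only before against after, or that the plan cannot show an effect over control; the document does not support either inference.

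A second reply is that knowledge items are binary, that an extension of McNemar's test (Bowker's) handles paired categories with more than two levels, and that a cut-point may sit in an analysis plan not shown here. This stands in part. Single knowledge items do suit McNemar, and a missing cut-point alone would not be a finding. But the article names McNemar for scores, and Bowker's extension, which is not mentioned, would suit single Likert items rather than a score.

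A third reply is that the worsening rates are not in the documents. That is correct: they are assumptions, hence the range. The result varies widely across it, but in every row the within-arm rate exceeds the 5% of the between-arm test.

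**Conclusion.** The point holds in a limited form. McNemar is the wrong test, as written, for the scores of both primary-outcome questionnaires; it would fit only items or outcomes that are truly binary. As a within-arm test it is also not evidence of superiority. With equal 15% improvement in both arms it is significant in 14% to 100% of simulated trials, depending on an assumed worsening rate of 10% down to 0%, against about 5% for the between-arm comparison. These percentages assume one independent binary result per pharmacy and no clustering. They illustrate how a within-arm test behaves and do not predict this trial's error rate.

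The between-group analysis is in the plan. What is lacking is a statement that it, and not the pre-post tests, decides effectiveness, together with wording in Data collection that agrees with it.

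**What to change.** 1. In Statistical methods, delete McNemar for the questionnaire scores. Keep it, if wanted, for genuinely binary paired items.
2. Report within-arm change in the scores descriptively, as a paired mean change with 95% CI.
3. State that effectiveness is decided by a between-arm comparison, and name it. Two choices are consistent with the text: the proportion improved, on which Sample size rests, or the between-arm score difference at T12. If the score difference is chosen, Sample size must be reconciled with it, because 30% against 15% improving does not give power for a difference in means. If the proportion is kept, define improved before the data are analysed.
4. Align the before-and-after sentence in Data collection, for example by saying that measurements are taken at T0 and T12 and that effectiveness is judged between groups.

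Cost: analysis wording only, with no change to data collection. The sample size stays at 121 (135) per group if the proportion improved is kept as the deciding measure; choosing the score difference would also require a revised justification of that number.

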### Data monitoring

The Trial Steering Committee (TSC) will be formed up of two researchers of trial, the general coordinator of the Coordinating Center of the Trial (CCT), and the administrative staff of the sponsor. The Pharmaceutical Promotion and Prevention research group will be the Coordinating Center of the Trial (CCT). This group is formed up of teachers, students, and graduates of pharmaceutical chemistry from the Faculty of Pharmaceutical and Food Sciences of the University of Antioquia. It will be in charge of the academic management and technical aspects of the study, also meeting spaces between researchers and sponsors. The person in charge of all aspects of the local organization, including the identification of possible recruits and consent, will be in charge of one of the members of the Pharmaceutical Promotion and Prevention research group, who will not be part of the study as a researcher.

The Data Monitoring Committee (DMC) will be the Technical Research Committee of the Research and Extension Center of the University of Antioquia, which is made up of teaching and administrative staff. The committee will perform the role of administrative management; the approval, control, and monitoring of financial resources; and the final compliance with the commitments of the trial. This committee will oversee the trial and request follow-up reports every 6 months, which will be done by two pharmacists of the Pharmaceutical Promotion and Prevention research group. A Stakeholder and Public Involvement Group (SPIG) will not be formed for this trial.

There are no planned interim analyses or “detention rules” specific to the study. Relevant agencies will be informed about the participation of pharmacy staff and pharmacies during their entire participation in the trial. We will adhere to international confidentiality and research practices and recommendations to monitor, audit, and administer the investigation. Due to the nature of the study, it is not necessary to make plans to collect, evaluate, report, and manage spontaneously requested and reported adverse events and other unwanted effects of trial interventions or behaviors. The periodic storage of the information in the database will show reports of the evaluation instruments, which will allow the monitoring of quality and data and generate reports according to the needs. The researchers involved in this study will be the only ones with access to the information. Every week, we will make a backup copy of the database on two different computers to protect the information.

## Limitations and potential bias

This study will use the simulated patient methodology as a tool to evaluate the skills and attitudes of customer service provided by pharmacy staff. This methodology has validity and reliability in pharmacy practice research [41]. To guarantee the quality of information, the simulated patients will receive training. Furthermore, a researcher will accompany the simulated patients on all visits to the drugstores and drugstores/pharmacies. The same researcher will make sure that the simulated patients complete the questionnaire immediately after each visit, thus controlling for common biases in this type of study. One possible limitation of our study is that the visits will not be recorded to minimize the possible biases associated with the collected information, as has been recommended by some systematic reviews [41].

## Discussion

We have planned this randomized trial to evaluate the effect of drugs with fiscalized substance (including controlled drugs) dispensation, health education, and pharmacovigilance continuing education programs in drugstores or drugstores/pharmacies. The intervention of this trial will be designed, developed, implemented, and evaluated, as a continuing education strategy to promote competencies in the proper utilization of drugs with fiscalized substances (including controlled drugs) in pharmacy staff, and therefore, it will contribute to reducing deficiencies in medical care. In Colombia, to our knowledge, this is the first controlled trial designed to assess pharmacy staff competencies.

Drugstores or drugstores/pharmacies play an essential role in the improvement of pharmacotherapy and patient outcomes, promotion of the rational use of drugs, and reduction of healthcare costs [42]. Besides, an employee eligible to work in an ambulatory (outpatient) pharmacy in Colombia is required to have one of the following educational levels (professional, technological, or technical). Besides, there are other empirical profiles called Drug Retailer (who does not have an educational level and is also called Drugstore Director). As a consequence, there is a large proportion of drugstores or drugstores/pharmacies that are managed by pharmacy staff who do not have the training and continuing education support [22, 43]. Recently, a cross-sectional, epidemiological study in Medellín (Colombia) drugstores or drugstores/pharmacies focused on the characterization of the use of drugs with fiscalized substances (including controlled drugs) and the pharmacy processes. Exactly 700 drugstores or drugstores/pharmacies were visited, and an equal pharmacy staff was interviewed. The most drugs with fiscalized substances dispensed without a valid medical prescription were amitriptyline 91.4% (640), tramadol 90% (630), and trazodone 60% (419). Around 60% of pharmacy staff do not have a technical or professional title, and their perception about the correct dispensing of drugs with fiscalized substances may be inadequate. A high percentage of the pharmacy staff perceives educational failures focused on the correct use of drugs [22].

Additionally, a systematic review describes different educational interventions with the support of ICTs and the effects on pharmaceutical knowledge and skills found. According to this review, they included 19 articles made mainly in developed countries. Most of the studies included in the review focused on evaluating the effect of continuing education programs on changing pharmacists’ knowledge and skills, and only one study evaluated the benefits of the program for patients or clients. The review authors conclude that there is insufficient evidence to support which methods from ICTs are the most effective and that it is necessary to intervene with robust, standardized, and validated methods [44].

A labor competence refers to a behavior that brings together different elements, performance criteria, and knowledge that determine the achievement, dominance, or fulfillment of the competence in a real work environment, which can be measured and evaluated, based on the combination of qualitative and quantitative research techniques, such as the observation and use of measuring instruments, respectively. Its measurement and evaluation should always be carried out jointly considering the combination of knowledge (what do you know?), skills (how do you do it?), and attitudes (how do you do it?). In this context, the pharmacy staff needs to improve their required competencies to contribute to the quality of drug dispensation, health education, and pharmacovigilance, in order to minimize medication errors and to help outpatients better manage their medicines. Continuing education, communication, and relationships with other health professionals are crucial to improving these competencies and, consequently, to achieve optimal patient medication management.

## Trial status

This study is currently in follow-up and intervention.

Protocol version: 0017102017MC. Registered on 28 November 2017.

Trial registration: NCT03388567.

Date of recruitment began on December 1, 2018.

Date of recruitment will be completed on December 31, 2019.

## Data Availability

The data sets generated and/or analyzed during the current study are not publicly available but are available from the corresponding author on reasonable request.

## Abbreviations

WHO: World Health Organization
FIP: Pharmaceutical International Federation
ICT: Information and Communication Technologies
CEP: Continuing education program
OR: Odds ratio
CIs: Confidence intervals
